## 3. OBJECTIVES

### 3.1 Primary Objectives:

3.1.1 Intervention: to determine which intervention (patient-level only vs. patient- and provider-level) is the most effective in increasing PrEP uptake.

3.1.2 Implementation Strategy: to measure the adoption of using electronic resources (e.g., computerized Gyn HIV Risk Tool integrated into an EHR and automated HIV test orders) in each clinic.

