There is no difference between Arms 2 and 3 regarding information and motivation. The difference between these two arms is the provider activity. We are trying to tease apart a clinic-based intervention that targets patients alone (Arm 2) versus both patients and providers (Arm 3). The primary outcome (behavior) is PrEP uptake, and this will be compared based on the Arm the patient is assigned, as is discussed in the data analysis plan. As competing interests (e.g., lack of time) and difficulty assessing the patient's HIV risk consistently have been listed as provider-level barriers to PrEP uptake; and patients do not perceive themselves to be at-risk of HIV, having these two arms will give us a lot of information about how to increase PrEP in women. For instance, Arm 2 will determine whether patients' awareness of their HIV risk will prompt them to ask their provider about PrEP or increase their desire to start PrEP; while Arm 3 will add an additional PrEP facilitator and determine if providers' awareness of their patients' HIV risk level will prompt them to discuss PrEP or increase PrEP uptake by patients.

**Figure 2. Study Schema.** There are two phases in the project. The first is to prepare documents, train staff, enroll providers and clinics. The second includes the clinical trial.

[figure not shown]

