## 8.3 Sample Size Estimate and Power.

A priori sample size calculation for the three-arm RCT was based on the expected annual patient volume across six clinics of approximately 7,800. We make the conservative assumption that 5-10% of these will score medium/high-risk on the Gyn HIV Risk Tool based on our preliminary studies, yielding 390 patients annually, with a total of 1,170 over three years of enrollment. Our estimate is conservative as we found that close to 70% of patients in one of our clinics scored medium/high, but these were adolescents and young adult women who have the highest prevalence of STIs and risk behaviors. These 1,170 patients will be seen by an expected 42 providers, where providers will be randomized to receive the potential intervention along with their patients. Given that patients using the same provider are not likely to be strongly related to each other in their choices for PrEP uptake (our co-primary outcome), we assume a low intra-provider correlation (IPC) of 0.01, with on average 28 patients per provider per year, yielding a design effect of  $1 + (28 - 1) * IPC = 1.27$ . Given these assumptions, if we estimate PrEP uptake at 6% (prelim data), we will be able to detect a difference of 9% (from 6 to 15%) between arms with 80% power. We will examine the intervention effect within specific race/ethnicity groups. We will include race and ethnicity in our minimizing of differences between arms at randomization, so we can assume that race and ethnicity will be similarly distributed across arms. Assuming we have approximately 50% non-Latinx Black patient participants (as we do for the general patient population), we expect to enroll 585 non-Latinx Black patients, allowing for 80% power to detect a difference of 6% in PrEP uptake in the standard of care arm to 15% in the intervention arms, assuming the same design effect of 1.27.

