JHU will conduct a cost-effectiveness analysis (CEA) from the perspectives of a payer or an adopting organization (e.g., Medicaid), and using standard analytical methods recommended by the Second Panel on Cost-Effectiveness Analysis. We will measure the relative efficiency of each active intervention (i.e., patient-focused intervention and patient-focused intervention plus EHR alerts) relative to standard of care in terms of their incremental cost-effectiveness ratios (ICER), calculated as the ratio of each intervention's incremental costs to its incremental benefits (e.g., incremental new STI/HIV test, new STI/HIV case diagnosed, number of new women on PrEP), and expressed in terms of dollars per health benefits. The ICER will be compared to a payer's "opportunity cost," i.e., willingness-to-pay (WTP) threshold to determine the intervention's acceptability in terms of its efficiency in generating health benefits, and under the particular implementation strategy. An ICER below the WTP will be indicative of good value for money produced by the intervention. Additionally, we will calculate the net monetary benefit and net health benefit of the intervention.

We will conduct a ROI by calculating the intervention's benefits, that is, the monetary values to the payer (or health care sector) of positive outcomes from the intervention (e.g., cost-offsets from avoided direct medical costs, as described above), minus its costs (i.e., incremental implementation costs, as measured above), expressed as a proportion of the incremental implementation cost.

We will estimate the total budget needed to finance each intervention strategy. We will calculate the incremental costs of the intervention for all those in need in the population covered by the payer, on a "per capita" basis, per unit of time (1 year). The population in need will be estimated by multiplying the prevalence of the condition by the total number of individuals covered by the payer.

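### Section 8.6 judges both active arms' cost-effectiveness only against standard of care, so Arm 3 can meet the value rule even when the provider alert's added cost does not

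*Protocol*

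**What the plan says.** Protocol section 8.6 describes the cost-effectiveness analysis. It takes the two active interventions (the patient-focused one, and the same with EHR alerts added) and assesses each "relative to standard of care in terms of their incremental cost-effectiveness ratios (ICER"), where the ICER is "calculated as the ratio of each intervention's incremental costs to its incremental benefits". The ratio is then set against the payer's WTP: "An ICER below the WTP will be indicative of good value for money produced by the intervention".

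Two other statements in the same section bear on the point. The analysis is to be done "using standard analytical methods recommended by the Second Panel on Cost-Effectiveness Analysis", and "we will calculate the net monetary benefit and net health benefit of the intervention". The section states no Arm 3 versus Arm 2 ratio, no ordering of the three strategies, no dominance step and no rule for preferring one arm.

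On the design, section 4 says of Arms 2 and 3 that "The difference between these two arms is the provider activity". Objective 3.1.1 is "to determine which intervention (patient-level only vs. patient- and provider-level) is the most effective in increasing PrEP uptake". Cost-effectiveness is a secondary endpoint (section 8.2.2).

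**The concern.** A payer or clinic would adopt one of three mutually exclusive strategies: usual care, the patient component, or the patient component with the alert. The strategies are nested, so what the alert buys is the step from Arm 2 to Arm 3. A ratio for Arm 3 against standard of care merges that step with the step from Arm 1 to Arm 2. If the patient component is cheap and does most of the work, it can carry an expensive alert under the threshold.

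At stake is how the economic result is read. Both arms could be reported as good value, with nothing in the stated rule showing that the second step costs more per added woman on PrEP than the payer is willing to pay.

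**Working it through.** The protocol gives no cost, ICER or WTP figure, so there is no stated result to reproduce. The check is algebraic, followed by illustrations.

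**Identity.** Let E1, E2 and E3 be uptake in the three arms, with E1 < E2 < E3. Let C2 and C3 be cost per PrEP-eligible patient over Arm 1. With w = (E2 − E1)/(E3 − E1):

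ICER(3 v 1) = C3/(E3 − E1) = w × ICER(2 v 1) + (1 − w) × ICER(3 v 2),

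where ICER(2 v 1) = C2/(E2 − E1) and ICER(3 v 2) = (C3 − C2)/(E3 − E2). So ICER(3 v 1) can lie below the WTP while ICER(3 v 2) lies above it.

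**Inputs from the protocol.** Section 8.3 says "we will be able to detect a difference of 9% (from 6 to 15%) between arms with 80% power". I use E1 = 6% and E3 = 15%. The 15% is the detectable level in the power statement, used here for Arm 3; it is not a forecast.

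**Assumed inputs.**
- WTP: $10,000 per additional woman on PrEP.
- Arm 2 uptake: 8, 10, 12 or 14%.
- Cost pairs (C2, C3): A = ($100, $700), B = ($200, $800), C = ($300, $600), D = ($400, $850).

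**Section 8.6 rule for Arm 3.** ICER(3 v 1) = C3/0.09, which gives A $7,778, B $8,889, C $6,667 and D $9,444. All are below $10,000, and none depends on Arm 2 uptake, so Arm 3 passes in all 16 scenarios.

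**Step by step.** Each cell shows ICER(2 v 1), then ICER(3 v 2).

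| Arm 2 uptake | A | B | C | D | ICER(3 v 2) above WTP |
|---|---|---|---|---|---|
| 8% | $5,000; $8,571 | $10,000; $8,571 | $15,000; $4,286 | $20,000; $6,429 | 0 of 4 |
| 10% | $2,500; $12,000 | $5,000; $12,000 | $7,500; $6,000 | $10,000; $9,000 | 2 of 4 |
| 12% | $1,667; $20,000 | $3,333; $20,000 | $5,000; $10,000 | $6,667; $15,000 | 3 of 4, one exactly at WTP |
| 14% | $1,250; $60,000 | $2,500; $60,000 | $3,750; $30,000 | $5,000; $45,000 | 4 of 4 |

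**One case in full (12%, pair B).**
- ICER(2 v 1) = 200/0.06 = $3,333.
- ICER(3 v 1) = 800/0.09 = $8,889, which passes.
- ICER(3 v 2) = 600/0.03 = $20,000, which does not.
- Identity: w = 0.06/0.09 = 2/3, and (2/3) × 3,333 + (1/3) × 20,000 = $8,889.
- Net monetary benefit against standard of care: Arm 2, 10,000 × 0.06 − 200 = $400; Arm 3, 10,000 × 0.09 − 800 = $100. Arm 2 is the better choice, although the rule passes both.

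**Break-even.** The alert is worth its cost when C3 − C2 is below WTP × (E3 − E2). At $10,000 that is $700, $500, $300 and $100 per eligible patient at Arm 2 uptake of 8, 10, 12 and 14%.

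**Where the stated comparator is right.** In five scenarios (8% with B, C, D; 10% with C, D) ICER(2 v 1) exceeds ICER(3 v 2). Arm 2 is then extendedly dominated, and standard of care is the proper comparator for Arm 3. None of the five gives a misleading result.

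**The case against.** The strongest reply is that section 8.6 already plans net monetary benefit. Against a common comparator, the Arm 3 minus Arm 2 difference equals WTP × (E3 − E2) − (C3 − C2), which is positive exactly when the alert is worth its cost. The section's singular wording is probably generic, so net benefit per arm is a fair reading. This stands in part: ranked by arm, net benefit would expose the problem. But the text states no ranking, and the only criterion it gives is the ICER against the WTP.

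A second reply is that the cited Second Panel methods may include a full incremental analysis. That source is not at hand, so this can be neither confirmed nor excluded. A general citation does not alter the comparator that the section names explicitly.

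Third, the ordering and dominance details could sit in an analysis plan, and ICER(3 v 2) can be derived from the planned increments. Both are true. The point rests on the comparator the protocol fixes, and no information is lost.

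Fourth, the inputs are assumed. Section 6.2.2 says existing alerts will be relaunched, which may keep the alert's added cost low and the problem absent.

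A reader might infer that the rule makes a false statement about Arm 3, or directs a payer to adopt it. The documents do not support that. An Arm 3 ICER below the WTP does mean good value against standard of care, and section 8.6 contains no adoption rule. Nor does objective 3.1.1 settle the matter, since it asks about effectiveness on PrEP uptake, not value.

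**Conclusion.** The point holds as an incompleteness in a stated analysis choice. With standard of care as the only comparator, the ICER rule cannot show whether adding the provider alert is worth its cost, and Arm 3 can pass when the alert alone would not. The algebra is certain, given that uptake rises from Arm 1 to Arm 2 to Arm 3.

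How often it would matter is not known. Under the assumed inputs it ranges from never at 8% Arm 2 uptake to always at 14%, so it is possible but not inevitable. It becomes more likely the more of the gain Arm 2 already delivers and the more the alert costs. The consequence is limited to a secondary economic endpoint. Randomisation, sample size and the primary PrEP comparison are unaffected.

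**What to change.** Amend the cost-effectiveness paragraph of section 8.6 to say that:

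- the three strategies are ordered by cost, dominated and extendedly dominated options are removed, and sequential ICERs are reported, including Arm 3 versus Arm 2 where both remain;
- the WTP is applied to that incremental ratio when choosing between arms, with the ratios against standard of care kept as descriptive results;
- net monetary benefit is reported for all three strategies over a range of WTP values, and the strategy with the highest value is preferred at a given WTP.

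The cost is a few sentences. The same cost and outcome data serve, and nothing in trial conduct changes.

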## 8.2 Secondary endpoints

**8.2.1** Intervention: Proportion of HIV test completion 4 weeks after clinic visit

**8.2.2** Implementation Strategy: cost-effectiveness, return on investment (ROI), budget impact, number clinics that complete assessments as intended

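### Section 8.6 calls an ICER below the willingness-to-pay threshold good value without requiring a positive incremental benefit, so read literally a costlier, less effective arm passes

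*Protocol*

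**What the plan says.** Section 8.6 of the protocol plans a cost-effectiveness analysis from the viewpoint of a payer or adopting organization, "using standard analytical methods recommended by the Second Panel on Cost-Effectiveness Analysis". For each active arm against standard of care, the ICER is "calculated as the ratio of each intervention's incremental costs to its incremental benefits". The benefit units are given as examples: new tests, new cases diagnosed and "number of new women on PrEP". The ratio is set against a "willingness-to-pay (WTP) threshold to determine the intervention's acceptability", and the criterion is that "An ICER below the WTP will be indicative of good value for money produced by the intervention". The next sentence reads "Additionally, we will calculate the net monetary benefit and net health benefit of the intervention", with no criterion attached. The section gives no incremental cost and no WTP value. Section 8.2 lists "cost-effectiveness, return on investment (ROI), budget impact" among the secondary implementation endpoints.

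**The concern.** The criterion uses only the ratio. It never asks whether the denominator is positive, and there is no step that sets aside an arm that is both costlier and less effective. A ratio of cost to benefit loses the information on which of the two is negative, so the comparison with the WTP means what the protocol intends only when the incremental benefit is positive. If an active arm costs more than standard of care and produces fewer PrEP starts, the criterion labels it good value, while the net monetary benefit says the opposite. The section ties acceptability to the ICER and gives no order of precedence. What is at stake is the conclusion drawn on one secondary endpoint. The primary comparison of PrEP uptake is not affected.

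**Working it through.** **Inputs.** Section 8.6 has no figure of its own to reproduce. The size of the trial comes from sections 8.3 and 8.4: 1,170 eligible women / 3 arms = 390 per arm; 14 providers per arm; 1,170 / 42 = 27.9, taken as 28 women per provider; intra-provider correlation 0.01. The design effect is 1 + 27 × 0.01 = 1.27, as stated. Control uptake is 6%: "if we estimate PrEP uptake at 6% (prelim data), we will be able to detect a difference of 9% (from 6 to 15%) between arms". The power attached to that sentence is not used here. Incremental cost and WTP are not given, so their ratio is varied as an assumption.

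**Sign of the ratio.** Let dC and dE be the incremental cost and benefit per eligible woman. The literal criterion is dC/dE < WTP. Net monetary benefit is NMB = WTP × dE − dC.

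- If dE > 0: dC/dE < WTP is the same as NMB > 0, so the two agree.
- If dE < 0: multiplying through by dE reverses the inequality, so dC/dE < WTP is the same as NMB < 0. The literal criterion then passes exactly the arms that net monetary benefit rejects.
- If dE = 0: the ICER is undefined.

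Illustration, with assumed values of $50 per woman and a WTP of $5,000 per PrEP start:

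- Costlier and less effective: dC = 50, dE = −0.02. ICER = 50 / −0.02 = −$2,500, which passes. NMB = 5,000 × (−0.02) − 50 = −$150 per woman.
- Cheaper and less effective: dC = −50, dE = −0.02. ICER = +$2,500, which passes. NMB = −100 + 50 = −$50 per woman.

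**How often this would occur.** Take a costlier arm, dC > 0, and write r = dC/WTP. The literal criterion passes if dE < 0 or dE > r; net monetary benefit passes only if dE > r. The gap between them is P(dE < 0), whatever r is.

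The standard error of dE at 6% in both arms is √(2 × 0.06 × 0.94 × 1.27 / 390) = 0.0192. Because the counts are small and ties occur, I used a beta-binomial simulation (14 providers × 28 women per arm, correlation 0.01, 200,000 trials, dC held fixed). With no true effect, dE is negative in 47.1% of trials, zero in 5.4% and positive in 47.5%. With a true fall from 6% to 4%, dE is negative in 85.9% and zero in 3.0%.

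Percentage of trials in which a costlier arm passes:

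| r = dC/WTP | No effect: ICER | No effect: NMB | 6% to 4%: ICER | 6% to 4%: NMB | 6% to 15%: either |
|---|---|---|---|---|---|
| 0.001 | 94.6 | 47.5 | 97.0 | 11.1 | 100.0 |
| 0.005 | 89.2 | 42.1 | 94.4 | 8.5 | 100.0 |
| 0.01 | 79.1 | 32.0 | 90.7 | 4.8 | 100.0 |
| 0.02 | 63.0 | 15.9 | 87.1 | 1.2 | 99.8 |
| 0.03 | 53.4 | 6.3 | 86.1 | 0.2 | 99.4 |
| 0.05 | 47.6 | 0.5 | 85.9 | 0.0 | 95.1 |
| 0.09 | 47.1 | 0.0 | 85.9 | 0.0 | 48.9 |
| 0.20 | 47.1 | 0.0 | 85.9 | 0.0 | 0.0 |

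For scale, $10 per woman at a WTP of $10,000 gives r = 0.001, and $50 at $5,000 gives r = 0.01.

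**The case against.** The paragraph does more than state this one criterion. It commits the analysis to established methods, it speaks of efficiency in generating health benefits, which presupposes that there are some, and it calls a low ICER indicative rather than decisive. It also plans net monetary and net health benefit, both of which are negative for a costlier, less effective arm, so the trial's own output would contradict a label of good value. A health economist would probably notice. All of this stands, and it makes the point small. It does not remove it: the method citation is general, and the only criterion written down is the one that fails when the benefit is negative.

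Three stronger readings are tempting, and the document does not support them.

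- A reader might infer that the criterion passes an ineffective arm in most trials. For a single comparison that depends on r: the rate exceeds one half only when r is below roughly 0.03 to 0.05, and the protocol gives neither cost nor WTP. The chance that at least one of the two active arms passes is higher, 64% to 99.7%, but that is a different event. Nor can the whole rate be charged to the flaw. Part of it is chance positive benefit, which net monetary benefit on point estimates shares; the sign problem adds a constant 47 points. The criterion was also never presented as a test with a controlled error rate.
- A reader might infer that the planned economic analysis as a whole cannot tell a useful arm from a harmful one. The planned net benefit measures can.
- A reader might infer that payers would be advised to adopt an arm on this criterion alone. Section 8.6 takes a payer's perspective but does not say that, and return on investment and budget impact are planned beside it.

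**Conclusion.** The point holds in limited form. As worded, the criterion gives the wrong answer whenever the estimated incremental benefit is negative and the arm costs more, and the text does not say that net monetary benefit overrides it. This is algebra and needs no assumption about costs beyond dC > 0 and a positive WTP.

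The frequencies rest on the planning inputs of sections 8.3 and 8.4, on PrEP starts as the benefit unit, and on a fixed positive incremental cost. Under these, a costlier arm with no effect is wrongly passed because of the sign in about 47% of trials, and one that lowers uptake from 6% to 4% passes in about 86% to 97%. If uptake truly rises to 15%, the two measures agree at every ratio tried, so a successful trial would not be misread. It is a minor correction to a secondary endpoint.

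**What to change.** In section 8.6, replace the criterion with wording to this effect: an intervention is good value if its incremental net monetary benefit, WTP × incremental benefit − incremental cost, is above zero. The ICER is reported and compared with the WTP only when incremental cost and incremental benefit are both positive. Otherwise the arm is described as dominant, dominated, or cost-saving with less benefit.

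How uncertainty in net monetary benefit is displayed can be left to the analysis plan. The cost is wording only, since net monetary benefit is already to be calculated and a WTP is needed under either criterion. The one downside is that a single ICER will not be reported in every case.

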## **7.4 Fidelity checks**

7.4.1 A research coordinator will observe the implementation of the study at the clinic and take field notes about the workflow, patients' questions, and providers' and stakeholders' concerns. The field notes will be analyzed every six months and used for cost analyses. Additionally, at every 6-month checks, the proportion of consecutive eligible patients who complete the eSHxForm will be assessed per clinic. If

completion is <75%, then research staff will obtain immediate feedback from clinical staff about barriers to completion and devise a plan to increase completion.

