## **14. LABORATORY EVALUATIONS**

### **14.1 Laboratory Evaluations and Specimen Collection**

None. All laboratory tests will be ordered and signed by providers and not the research team.

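### The ROI rule in 8.6 counts the payer's savings from positive outcomes but charges only implementation cost; read literally, it omits the payer's PrEP care spending and overstates ROI.

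*Protocol*

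**What the plan says.** Section 8.2 names "cost-effectiveness, return on investment (ROI), budget impact" among the secondary implementation endpoints. Section 8.6 sets the perspective of the cost-effectiveness analysis, "from the perspectives of a payer or an adopting organization (e.g., Medicaid"), and lists as examples of benefit for the cost-effectiveness ratio "incremental new STI/HIV test, new STI/HIV case diagnosed, number of new women on PrEP".

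Section 8.6 then gives ROI its own formula. The benefit term covers "the monetary values to the payer (or health care sector) of positive outcomes from the intervention (e.g., cost-offsets from avoided direct medical costs"), with a reference back to an earlier description of those offsets. From it the plan subtracts the costs: "minus its costs (i.e., incremental implementation costs, as measured above), expressed as a proportion of the incremental implementation cost".

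Two other places bear on what cost means here. Section 7.4 says of the fidelity observations: "The field notes will be analyzed every six months and used for cost analyses". Section 14.1 says: "All laboratory tests will be ordered and signed by providers and not the research team". For the cost-effectiveness ratio and the budget impact, section 8.6 refers to incremental costs without listing what they contain.

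**The concern.** The trial aims to raise PrEP prescribing. From a payer's side, any saving that follows from more PrEP is obtained by paying for the drug, the tests required before starting it and the associated visits. The ROI rule credits the saving. It then defines cost, with an i.e. and not an e.g., as implementation cost alone, so the spending that produces the saving appears on neither side.

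A strategy that costs the payer more than it saves could then be reported, under a named secondary endpoint, as a positive return.

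**Working it through.** **1. Is there a figure to reproduce?** No. The protocol states no ROI value, unit cost or savings figure. The check is therefore algebraic, followed by an illustration on labelled assumptions.

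**2. The written rule.** Let B be the benefits, Ci the incremental implementation cost and Cd the payer's incremental PrEP drug, laboratory and visit cost.

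- As written: ROI = (B - Ci)/Ci = B/Ci - 1.
- Cd netted from benefits, denominator unchanged: ROI = (B - Cd - Ci)/Ci = B/Ci - 1 - Cd/Ci. Overstatement: Cd/Ci.
- Cd added to cost in both terms: ROI = B/(Ci + Cd) - 1. Overstatement: B/Ci - B/(Ci + Cd).

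Both overstatements are above zero whenever Cd and B are positive. The two corrected forms always share the same sign, that of B - Ci - Cd. So where B exceeds Ci, the written rule shows a gain and the corrected rule a loss once Cd exceeds B - Ci.

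**3. Unit-free illustration** (ratios assumed).

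| B/Ci | Cd/Ci | Written ROI | Cd netted from benefits | Cd in both terms |
|---|---|---|---|---|
| 2 | 0.25 | +1.00 | +0.75 | +0.60 |
| 2 | 0.5 | +1.00 | +0.50 | +0.33 |
| 2 | 1 | +1.00 | 0.00 | 0.00 |
| 2 | 2 | +1.00 | -1.00 | -0.33 |
| 3 | 0.25 | +2.00 | +1.75 | +1.40 |
| 3 | 0.5 | +2.00 | +1.50 | +1.00 |
| 3 | 1 | +2.00 | +1.00 | +0.50 |
| 3 | 2 | +2.00 | 0.00 | 0.00 |

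**4. Scale, using section 8.3.** There are 1,170 PrEP-eligible patients, so 1,170/3 = 390 per arm if they divide evenly. The uptake contrast is 15% - 6% = 9 percentage points, and 390 x 0.09 = 35.1 extra users per active arm. With an assumed payer cost per user, the omitted Cd is:

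- $500: 35.1 x 500 = $17,550
- $5,000: 35.1 x 5,000 = $175,500
- $20,000: 35.1 x 20,000 = $702,000

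**5. One worked case.** Assume Ci = $100,000 and B = $150,000. Written ROI = 150,000/100,000 - 1 = +50%, whatever PrEP care costs. With Cd in both terms:

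- $500 per user: 150,000/117,550 - 1 = +28%
- $5,000 per user: 150,000/275,500 - 1 = -46%
- $20,000 per user: 150,000/802,000 - 1 = -81%

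The sign changes at Cd = 150,000 - 100,000 = $50,000, or 50,000/35.1 = about $1,425 per user.

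**6. Could the text already include Cd?** Both the cost term and the benefit term of the ROI sentence refer back to material above them. In the text available, no earlier section measures costs or describes offsets. The only cost data source named is the section 7.4 field notes, which record clinic workflow. The laboratory tests are ordered in clinical care (section 14.1). No passage charges PrEP care to ROI.

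**The case against.** The strongest reply is that the cost scope is undefined rather than wrongly defined. Both back-references lead nowhere, so PrEP care might have been meant as part of implementation cost, or the offsets might have been meant net of it. On either reading the overstatement disappears, and costing detail often sits in an analysis plan. This stands as a caveat but does not rescue the sentence. The protocol fixed the formula here instead of deferring it. Positive outcomes and avoided costs describe gross savings, and the i.e. limits cost to implementation. If the wider meaning is intended, the sentence still has to say so.

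A second reply is that return on implementation spending is a legitimate quantity. That is correct. The denominator can stay, provided the benefits are net of PrEP care.

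Four stronger readings are tempting, and the document does not support them:

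- **PrEP care is the payer's largest added cost.** No cost data are given. At the low assumption it is only $17,550.
- **The error favours the more effective arm.** It depends on Cd/Ci, and Arm 3 adds provider alerts (section 4), so its Ci may also be higher. The effect on ranking is not determined.
- **The overstatement can be enormous.** Dividing $702,000 by an assumed $25,000 implementation cost gives 28, but only if Cd is charged in the numerator alone. With Cd in both terms and B = 1.5 x 25,000 = $37,500, ROI moves from +0.50 to 37,500/727,000 - 1 = -0.95, a change of about 1.45.
- **About 35 extra users are expected.** Section 8.3 gives 6% versus 15% as a detectable difference, not a forecast.

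Finally, ROI is not the only value measure. Section 8.6 also plans a cost-effectiveness ratio, net benefit and budget impact. That limits the consequence, but ROI is named separately and has its own cost definition.

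**Conclusion.** The point holds for the rule as written. Followed literally, section 8.6 overstates ROI for any positive PrEP care cost and any positive benefit, and it can report a gain where the payer loses. The direction follows from the algebra, given that literal reading.

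The size cannot be derived from the protocol. The range of $17,550 to $702,000 omitted per arm rests on an even split of patients, the detectable difference in section 8.3 and an assumed $500 to $20,000 per user. The ROI percentages rest further on assumed benefits and implementation cost. None of these is an estimate of what the trial will find.

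The rule should be corrected, but it touches a secondary implementation endpoint only. The primary PrEP comparison is unaffected.

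**What to change.** In section 8.6, choose one of two forms and state it:

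- net the incremental PrEP drug, laboratory and visit costs borne by the payer out of the benefits, keeping implementation cost as the denominator; or
- add those costs to implementation cost in both numerator and denominator.

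Either way, count these costs over the same horizon as the cost offsets, and state that horizon. Replace the two back-references with an explicit list of cost categories. Apply the same cost scope to the cost-effectiveness ratio and the budget impact.

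The data burden is modest. Table 1 already plans to collect PrEP prescriptions as a discrete record element and continuation at 3, 6 and 9 months; unit costs would have to be added. Because continuation is followed only to 9 months and no horizon is given for the offsets, matching the two may need some modelling. The reported ROI will be less favourable.
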